**Method/Design:**

One thousand (n = 1000) 16-18 year-old girls will be invited to participate in an HPV vaccination programme: Five-hundred (n = 500) will have received a previous invitation to get vaccinated but will have failed to do so (previous non-attenders) and 500 will not have previously received an invitation (first-time invitees). Girls will be randomly selected from eligible participants who are registered with a GP in areas covered by the Birmingham East and North (BEN) and Heart of Birmingham Primary Care Trusts. The two samples of girls will be randomised to receive either a standard vaccination invitation letter or an invitation letter including the offer of vouchers worth £45 for receiving three vaccinations. Girls will also complete a questionnaire to assess the quality of their decisions to be vaccinated. The primary outcome will be uptake of the 1^st^ and 3^rd^ vaccinations. The secondary outcome will be the quality of the decisions to undertake the vaccination, measured by assessing attitudes towards and knowledge of the HPV vaccination.

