### Objectives and hypotheses

The primary objectives of the present study are:

(a) To assess the impact of financial incentives on the initial uptake (uptake of the first vaccination) and completion rates (uptake of the third vaccination) of an HPV vaccination programme.

(b) To assess the impact of financial incentives on the quality of the decision to be vaccinated as measured by attitudes towards and knowledge of the vaccination.

The secondary objective is:

(a) To assess whether the impact of financial incentives on the initial uptake and completion rates of an HPV vaccination programme is moderated by participants’ levels of social deprivation.

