### Sample size determination

According to the latest report from the Department of Health on coverage of the HPV vaccinations [7], the average completion rate for the “catch-up” campaign targeting females aged 17-18 years in the Birmingham East & North Primary Care Trust is 32.4%. Previous studies investigating the impact of financial incentives on uptake of vaccinations have reported an avergage between-group difference of approximately 8.5%: Specifically, Moran et al. [17] reported an effect size of 8.5% for uptake of the influenza vaccination with incentives (20.3% (control group) vs 28.8% (incentivised group)) and Yokley et al. [18] reported an avergage increase of 8.4% in childhood immunisation across three time points with the addition of inventives (at two weeks: 10.1% (control group) vs. 22.5% (incentivised group); at 2 months: 22.7% (control group) vs. 30.8% (incentivised group); at three months: 26% (control group) vs 30.8% (incentivised group)). Based on these figures, we expect financial incentives in this study to increase completion (i.e. uptake of the 3^rd^ vaccination) of the HPV vaccination programme by 8.5%, resulting in a completion rate of 40.9% by incentivised groups. To detect this difference between arms using a two-tailed *χ*^2^ test at the 5% significane level with 80% power, a sample of 1008 participants is required (calculations performed in GPower 3.0); This figure has been rounded off to the nearest whole number, resulting in a required sample of 1000 participants (half of whom consist of previous-non attenders and half of whom, first-time invitees), giving 500 in each intervention arm (See Table 1).

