### Statistical analysis

To assess the impact of the intervention on initial uptake (i.e. the 1st vaccination) and completion of the HPV vaccination programme (i.e. the 3rd vaccination) logistic regressions will be performed separately for each of the two samples, i.e. for girls who have not received an invitation to get vaccinated before and those who have received a previous invitation but have failed to attend. To test the moderating effect of social deprivation on the impact of the intervention, the interaction between IMD scores and intervention will be added to the logistic regression models. To test whether there is a difference in the size of effect of the intervention in the two samples, datasets will be combined and another logistic regression conducted, in which whether participants have received an invitation to get vaccinated before or or not will be added as a predictor to the model, along with the intervention. To test for differences in the attrition rates between the 1^st^ and 3^rd^ vaccinations between the invervention and control groups the *χ*^2^ test will be used. Finally, differences in knowledge of the HPV vaccination between intervention and control group will be tested using the *χ*^2^ test, while differences in attitudes towards the HPV vaccination will be examined via a one-way analysis of variance. All tests will be assessed at the 5% level of significance.

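### Dose-1 uptake and completion are both primary and each is tested in both samples at a full 5%, with no order or success rule, and decision quality is ranked inconsistently

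*Protocol article*

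**What the plan says.** The abstract (Method/Design) names uptake of the first and of the third vaccination as the primary outcome. Objective (a) under Objectives and hypotheses, and Hypothesis I, name the same two doses. Neither is ranked above the other.

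Statistical analysis plans a logistic regression for each dose in each of the two samples, which makes four tests of the incentive on primary outcomes. The section closes with "All tests will be assessed at the 5% level of significance".

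Sample size determination rests on a single comparison, completion with the two samples pooled. The control rate "in the Birmingham East & North Primary Care Trust is 32.4"%, and the effect is an 8.5-point rise, "resulting in a completion rate of 40.9% by incentivised groups". For a two-sided χ² comparison of the arms, the section gives this requirement: "test at the 5% significane level with 80% power, a sample of 1008 participants is required". This is rounded to 1000, "giving 500 in each intervention arm".

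On decision quality, the abstract says "The secondary outcome will be the quality of the decisions to undertake the vaccination". Objectives and hypotheses places "To assess the impact of financial incentives on the quality of the decision to be vaccinated" second in the list of primary objectives.

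**The concern.** Four tests at a full 5% each can produce a nominally significant primary result more often than 5% of the time when incentives do nothing. The document has no gatekeeping, no split of alpha and no requirement that both doses succeed. One significant dose in one sample could therefore be reported as the trial's finding without breaking any stated rule.

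The four tests are also not the test the trial was sized for. Each by-sample test has half the planned number of girls.

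The inconsistent rank of decision quality leaves it unclear whether the knowledge and attitude tests also count as primary. That matters because Hypothesis III predicts harm on this outcome. The Discussion expects the results to inform debate on using incentives for health promotion, so what counts as the main finding should be settled beforehand.

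**Working it through.** **1. The plan's own sample size.** Inputs from Sample size determination: p₁ = 0.324, p₂ = 0.409, difference 0.085, two-sided α = 0.05, power 0.80. The mean rate is p̄ = 0.3665.

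n per arm = [1.96·√(2p̄(1−p̄)) + 0.842·√(p₁(1−p₁)+p₂(1−p₂))]² / 0.085² = (1.336 + 0.571)² / 0.007225 ≈ 503.3, rounded up to 504. The total is 1008, as stated. The design therefore supports one pooled comparison at 5%.

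**2. Power of the planned tests.** Same rates, no continuity correction:

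| Comparison | n per arm | α | Power |
|---|---|---|---|
| Completion, samples pooled | 500 | 0.05 | 79.7% |
| Completion, one sample | 250 | 0.05 | about 50% |
| Completion, one sample, Bonferroni over four tests | 250 | 0.0125 | about 30% |

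**3. Correlation between the two doses.** The Procedure section allows no skipping of doses, so completers are a subset of dose-1 attenders. For nested binary outcomes with rates a (dose 1) and b (dose 3), the correlation is φ = √[b(1−a) / (a(1−b))].

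- England catch-up rates from the Background, 62.2% and 31.8%: φ = √(0.318×0.378 / (0.622×0.682)) = √(0.1202/0.4242) = 0.53.
- Lower rates, assumed here as 30% and 20%: φ = √(0.2×0.7 / (0.3×0.8)) = √(0.14/0.24) = 0.76.

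The protocol does not give the rates expected in either sample, so both pairs are assumptions.

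**4. Chance of at least one false positive.** The two test statistics within a sample are treated as bivariate normal with correlation φ, and no effect exists anywhere. Let e be the chance that at least one is significant. The samples are independent and separately randomised (Trial design), so over both the chance is 1 − (1−e)².

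| | Per sample | Both samples |
|---|---|---|
| Two-sided, 62.2%/31.8% | 9.0% | 1 − 0.910² = 17.2% |
| Two-sided, 30%/20% | 8.0% | 1 − 0.920² = 15.4% |
| False benefit only, 62.2%/31.8% | 4.5% | 1 − 0.955² = 8.8% |
| False benefit only, 30%/20% | 4.0% | 1 − 0.960² = 7.9% |

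A simulation with 250 per arm per sample gave two-sided figures of 17.0% and 15.2% over both samples. Four independent tests would give 1 − 0.95⁴ = 18.5%. If the two doses were perfectly correlated, the figure over both samples would still be 1 − 0.95² = 9.75%.

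A single two-sided 5% test gives 5% in total and 2.5% for false benefit.

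**The case against.** **The success rule.** The inflated figures require that any one significant result counts as success, and the document does not say so. The abstract speaks of one primary outcome covering both doses, and Hypothesis I joins them with "and". If both doses had to be significant, there would be no inflation within a sample. This stands as a limit on the figures. It does not remove the problem, because the both-doses rule is not stated either.

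**Separate populations.** The two samples differ and are separately randomised, so each may be read as its own question. On that reading the relevant figures are those per sample, about 8-9% two-sided and 4-4.5% for false benefit. They are still above 5% and 2.5%.

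**Direction.** The two-sided figures include false findings that incentives reduce uptake. For the risk of a false success, the benefit-only rows apply, and they are about half as large.

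**Detail left to an analysis plan.** A multiplicity procedure is often placed there. But this protocol applies 5% to every test, so an analysis plan that set reduced levels would depart from its wording. Sizing on completion hints at a lead outcome but sets no testing order.

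**A stronger reading.** A reader might infer a false-claim risk of about 25%, by adding the knowledge and attitude tests: 1 − 0.828 × 0.95² = 25.2%. The documents do not support that as the main figure. It needs decision quality to be primary, which the abstract contradicts. It needs exactly two such tests, independent of each other and of uptake, although both measures come from the same attending girls. It also mixes a benefit hypothesis with a harm hypothesis.

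**Conclusion.** The point holds. As written, the plan does not control the chance of a false primary claim across the two doses, and it does not say what would make the trial positive.

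The size is that shown in the table: roughly 8-9% per sample and 15-17% overall two-sided, with about half of that for false benefit. It assumes no true effect, an any-one-result success rule, and dose rates within the range used. The 15-17% also requires counting errors across both samples as one family.

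Two further points need no such assumptions. The by-sample tests named for the primary outcomes are not the pooled test behind the sample size. And the abstract and the objectives disagree on the rank of decision quality. This should be corrected, but it does not undermine the trial's design.

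**What to change.** In Statistical analysis, name completion (third vaccination) as the single primary test at 5%, in the combined logistic model with sample as a stratum. That section already plans a combined model with previous invitation as a predictor. The contrast is the one the trial was sized on, with 79.7% power at 500 per arm if the planned rates hold.

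Test dose-1 uptake in the same model at 5% only if completion is significant. Report the by-sample effects on both doses as estimates with confidence intervals, labelled secondary. Label decision quality as secondary in both the abstract and Objectives and hypotheses.

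The cost is more than wording. The pooled effect replaces the two by-sample effects as the main estimate. Neither dose-1 uptake alone nor a result in one sample could make the trial positive. If completion misses significance, which would happen about 20% of the time even if the planned effect is real (1 − 0.797), dose-1 uptake gets no formal test. Keeping all four tests under Bonferroni would preserve the by-sample claims, but at about 30% power each for completion.

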## Discussion

The results of the study will produce valuable information regarding the potential effectiveness of financial incentives in increasing uptake and completion of the HPV vaccinations by teenage girls. The results will also provide valuable information regarding the validity of concerns about the potentially adverse effects of financial incentives on the quality of people’s decisions to engage in incentivised behaviours. If evidence from this trial supports such concerns, further research will be needed to assess how incentives might undermine informed choice, e.g. whether they alter who attends or whether they alter the attitudes towards and/or knowledge of the target behaviour in all who are offered incentives and therefore in those who attend. The design of the present trial does not allow for such assessments to be made.

Knowledge regarding the impact of financial incentives both on uptake of the HPV vaccination and on the quality of decisions to engage in incentivised behaviours is lacking in the literature. Findings therefore, are expected to clarify these issues and have the potential to inform discussions concerning the increasing use of financial incentives for health promotion.

### Research governance

The trial is run by the Birmingham East and North Primary Care Trust, in partnership with the Young Foundation, as part of the former’s service development. In consultation with the Trust, it was deemed that ethical approval was not required for its implementation. Ethical Approval was sought for researchers at King’s College London, Centre for the Study of Incentives in Health, to access data from the Birmingham East and North Primary Care Trust in order to evaluate the financial incentives scheme. This was granted by the Birmingham East and North Research Ethics Committee (reference 11/WM/0073, 8^th^ April 2011). NHS Permission for Research was granted by the Birmingham and the Black Country Comprehensive Local Research Network (BBC CLRN) Research Management & Governance (RM&G) Consortium Office on behalf of the BBC CLRN RM&G Consortium Trusts (reference BENPC040.44791, 1^st^ August 2011**).**

### Trial registration

Current Controlled Trials, ISRCTN52339409.

